## Abstract

**Background:**

People with severe mental illness demonstrate markedly reduced life expectancy, largely due to preventable cardiometabolic disease. This burden is particularly pronounced in compulsory forensic psychiatric care, where prolonged inpatient stays, restrictive environments, and long-term antipsychotic treatment contribute to high levels of sedentary behavior, unhealthy diet, tobacco use, and metabolic disturbances. Despite substantial cardiometabolic risk, individuals in forensic psychiatric settings are frequently excluded from preventive health research, resulting in limited evidence regarding the feasibility and acceptability of lifestyle interventions in this context. Recent international recommendations emphasize the need to integrate structured lifestyle interventions as core components of mental healthcare, including in secure and compulsory settings.

**Objectives:**

The FOR-HEALTH study aims to assess the feasibility and acceptability of an adapted Structured Health Dialogue intervention delivered in compulsory forensic psychiatric inpatient care. Secondary objectives are to describe cardiometabolic, lifestyle, and patient-reported outcomes to inform the design of a future definitive randomized controlled trial.

**Methods:**

This randomized controlled feasibility trial evaluates an adapted version of Structured Health Dialogues, an evidence-based cardiovascular prevention model originally developed for Swedish primary care. Participants are randomized in a 1:1 ratio to receive either Structured Health Dialogues plus treatment as usual or treatment as usual alone. Structured Health Dialogues integrate a systematic assessment of lifestyle behaviors, biological risk markers, psychosocial stress, and heredity into an individualized visual risk profile, which forms the basis for a motivational, person-centered dialogue. The intervention is adapted to the forensic psychiatric context and delivered within a secure inpatient setting. Primary outcomes relate to feasibility, including recruitment, retention, intervention delivery, and acceptability. Secondary outcomes include exploratory changes in lifestyle behaviors, cardiometabolic risk markers, and patient-reported outcomes. A total of 50 participants (25 per group) will be recruited. The study has been approved by the Swedish Ethical Review Authority. The findings are expected to inform the design and implementation of a future definitive randomized controlled trial evaluating Structured Health Dialogues in forensic psychiatric inpatient care.

**Trial registration:**

NCT07157813.

## Strengths and limitations of this study

### Strengths

#### High clinical relevance

The study addresses a well-documented physical health inequality among individuals with severe mental illness in compulsory forensic psychiatric care, a population that remains underrepresented in preventive health research.

#### Manualized, theory informed intervention

Structured Health Dialogue is a standardized, evidence-based intervention integrating cardiometabolic risk assessment, motivational interviewing, and visual risk communication, supporting reproducibility and future implementation.

#### Person-centered focus in a coercive context

Despite being conducted within compulsory forensic psychiatric care, the intervention explicitly emphasizes autonomy, shared decision-making, and individualized goal setting, addressing key ethical challenges in forensic psychiatric settings.

#### Pragmatic design

The trial is embedded in routine forensic psychiatric inpatient care, enhancing ecological validity and relevance for future scale up and real-world implementation.

#### Comprehensive outcome framework

Feasibility outcomes are combined with objective cardiometabolic measures and validated patient-reported outcomes, allowing assessment of both implementation processes and clinically relevant secondary outcomes.

## Limitations

### Single-center setting

Findings may have limited generalizability to other forensic psychiatric contexts with different organizational structures or patient populations.

### Feasibility-oriented primary aim

Although a power calculation was performed to enable detection of changes in selected secondary outcomes, the study is primarily designed to evaluate feasibility and acceptability. As such, findings related to clinical outcomes should be interpreted cautiously.

### Open-label design

Blinding of participants and clinicians is not feasible, which may introduce performance or expectancy bias.

### Contextual constraints

The secure inpatient environment may restrict participants’ ability to independently implement and sustain lifestyle changes beyond the intervention context.

### Limited long-term follow-up

Outcomes are assessed up to 12 months; longer-term sustainability of behavioral and metabolic changes cannot be determined.

## Introduction

### Background and rationale

People living with severe mental illness (SMI), including schizophrenia spectrum disorders, bipolar disorder, and major depressive disorder, have substantially reduced life expectancy and poorer physical health than the general population. The estimated mortality gap is approximately 15–20 years, with recent meta-analytic evidence confirming persistently increased mortality in schizophrenia and related disorders [1–4]. This excess mortality is largely driven by somatic diseases rather than external causes, with cardiovascular disease representing a major contributor to the mortality gap [5].

Cardiometabolic risk factors are highly prevalent among individuals with SMI. Metabolic syndrome, a cluster of metabolic abnormalities that increases the risk of both type 2 diabetes and cardiovascular disease, occurs substantially more frequently in people with SMI than in the general population [6, 7]. Diabetes mellitus is also more common among individuals with SMI [8] and data from the Swedish National Forensic Psychiatric Quality Register further illustrate the magnitude of this metabolic burden in forensic psychiatric populations, showing that diabetes is approximately 6.7 times more common among men and 9 times more common among women receiving forensic psychiatric care compared with the age-matched general population [9].

The excess physical health burden in SMI is widely recognized as multifactorial. Long-term exposure to psychotropic medication, particularly second-generation antipsychotics, is associated with weight gain and metabolic disturbances [10, 11]. Sedentary behavior is common among people with severe mental illness [12, 13], dietary patterns are often characterized by poor nutritional quality [14], and tobacco use remains highly prevalent [15]. Recent meta-reviews further support the efficacy and implementation of lifestyle and physical activity interventions as adjunctive treatments in severe mental illness [16].

Despite the high prevalence of modifiable risk factors, preventive somatic healthcare remains insufficiently integrated into routine psychiatric care. People with SMI are more likely to live with multiple coexisting physical health conditions (physical multimorbidity) [17] yet are less likely to receive systematic cardiovascular risk assessment and coordinated management of these conditions. Addressing physical health has therefore increasingly been recognized as an essential component of treatment and rehabilitation within psychiatric and forensic psychiatric services [18].

The Lancet Psychiatry Commission highlighted protection of physical health as a core component of mental healthcare [19]. More recently, the third report of the Lancet Psychiatry Physical Health Commission emphasized the need to implement structured interventions targeting physical activity, diet, and smoking within routine mental health services [20]. WHO recommendations similarly support integrating preventive physical healthcare into services for people with SMI [21].

Individuals receiving forensic psychiatric care typically present with complex SMI, most commonly schizophrenia spectrum disorders, often accompanied by substance use disorders and other psychiatric comorbidities [22]. These patients have committed criminal offenses in the context of SMI and receive compulsory treatment within secure psychiatric services where care is shaped by both therapeutic needs and considerations of risk and public safety. Registry data from Sweden further indicate substantial somatic health needs among individuals in forensic psychiatric care as well as long treatment trajectories within these services [23, 24]. Recent cohort and registry-based studies have also highlighted elevated mortality and adverse outcomes in forensic psychiatric populations [25, 26].

However, evidence regarding effective lifestyle interventions in forensic psychiatric populations remains limited. A systematic review concluded that although unhealthy lifestyle behaviors are common among forensic mental health service users, intervention studies targeting these behaviors in forensic settings remain scarce [27]. At the same time, initiatives aimed at improving somatic healthcare in forensic psychiatric settings are emerging. Recent work has explored the integration of primary care within specialized forensic psychiatric services [28], and intervention-oriented research is beginning to develop, including feasibility trials of structured weight management and lifestyle interventions [29, 30].

Structured Health Dialogues (SHD) represent a person-centered preventive approach developed for Swedish primary care. The method combines systematic assessment of lifestyle behaviors and biological risk markers with an individualized visual risk profile that supports dialogue and goal setting. Population-based evidence suggests that SHD may improve cardiovascular risk profiles and contribute to reduced mortality [31]. However, to our knowledge, SHD has not previously been evaluated in forensic psychiatric populations. Although SHD was originally developed and evaluated in Swedish primary care, implementation in compulsory forensic psychiatric inpatient care presents unique challenges. Compared with primary care, forensic psychiatric care is characterized by secure environments, restricted patient autonomy, and institutional routines that may influence both the delivery of the intervention and patients’ opportunities to modify lifestyle behaviors. Consequently, adaptation of both the intervention and the study procedures is required. A randomized controlled feasibility trial is therefore warranted to evaluate the feasibility and acceptability of the intervention and study procedures before conducting a future definitive randomized controlled trial. The overall aim of the FOR-HEALTH project is to improve the physical health of forensic psychiatric inpatients by developing and evaluating structured lifestyle interventions. The present randomized controlled feasibility trial aims to evaluate the feasibility and acceptability of implementing Structured Health Dialogues (SHD) in forensic psychiatric inpatient care and to generate data that will inform the design of a future definitive randomized controlled trial through exploratory evaluation of clinical outcomes.

## Aims and objectives

### Primary aim

To assess the feasibility and acceptability of SHD as a complement to treatment as usual (TAU) in forensic psychiatric inpatient services.

### Secondary aims

To describe cardiometabolic, lifestyle, and patient-reported outcomes, including potential changes in a composite cardiometabolic risk profile derived from SHD (the Swedish “health curve”), as well as metabolic risk markers.

## Methods and analysis

### Study design and setting

This study is a single-center, parallel-group, randomized controlled feasibility trial. The design and reporting follow methodological guidance for pilot and feasibility studies and adhere to the CONSORT 2010 statement and its extension for randomized pilot and feasibility trials [32, 33]. Participants are randomized in a 1:1 ratio to receive either SHD in addition to TAU or TAU alone. A total of 50 participants (25 per group) will be recruited.

The overall flow of participants through the study, including enrollment, allocation, follow-up, and analysis, is illustrated in the CONSORT flow diagram (Fig. 1).

**Fig. 1 Fig1:**
[figure not shown]
CONSORT flow diagram illustrating participant enrollment, randomization, follow-up, and feasibility analysis in the FOR-HEALTH trial

### Study setting

The trial is conducted at a large forensic psychiatric clinic in Sweden, providing compulsory inpatient care under the Swedish Forensic Psychiatric Care Act. Patients admitted to forensic psychiatric care have been convicted of criminal offenses and have been found to suffer from an SMI at the time of the offense. Therefore, they are sentenced to forensic psychiatric care rather than imprisonment. Care is individualized and may continue for several years depending on the patient’s psychiatric condition and the assessed risk of serious reoffending. The current clinic provides care across all three national security levels (levels 1–3), reflecting the full spectrum of Swedish forensic psychiatric inpatient care [24].

### Participants

#### Inclusion criteria

Adult age, 18–64 yearsAdmitted to forensic psychiatric inpatient care at the participating clinicCapacity to provide informed consent

#### Exclusion criteria

Severe language barriers precluding meaningful participationSevere cognitive impairment precluding informed consentAcute psychiatric instability (e.g., acute psychosis or high suicide risk)Severe aggression or behavioral disturbance preventing safe participation

### Recruitment and consent

Potential participants are identified by clinical care teams and informed about the study. Written and verbal information is provided by the research team, and written informed consent is obtained prior to baseline assessments. Participation is voluntary and may be withdrawn at any time without consequences for ongoing care or legal status.

### Randomization and blinding

Randomization is performed after completion of baseline assessments using a computer-generated randomization sequence with block randomization, stratified by ward security level (security classes I–III). Stratification by ward security level was chosen because patients treated in different security levels may differ regarding psychiatric severity, level of supervision, access to rehabilitation activities, and opportunities to engage in lifestyle-related interventions, all of which may influence the feasibility and delivery of the intervention. Participants are not matched, as randomization is considered sufficient to ensure group comparability in this feasibility trial. An independent digital randomization table is generated using a secure web-based randomization service (www.sealedenvelope.com) to ensure allocation concealment prior to assignment.

The randomization sequence is generated in advance and implemented by a member of the research team not involved in recruitment or baseline assessment. Due to the nature of the intervention, the study is open label. Where feasible, data analysis will be conducted without knowledge of group allocation.

### Intervention

#### Structured Health Dialogues (SHD)

Participants allocated to the intervention group receive two nurse-led SHD sessions over a 12-month period. The first session is delivered at baseline following randomization, and the second session at 12-month follow-up. Participants in the intervention group also complete the scheduled follow-up assessments at 6 months, including anthropometric measurements, blood sampling, and patient-reported outcome measures. These assessments are performed to evaluate participant retention, completeness of data collection, and the feasibility of repeated outcome assessments, while also providing exploratory longitudinal outcome data. No additional SHD is delivered at the 6-month follow-up. Between study visits, participants continue to receive routine forensic psychiatric care according to local clinical practice, including standard psychiatric and medical care as clinically indicated. The SHD is intended to complement this ongoing care by providing individualized cardiovascular risk visualization and a structured person-centered dialogue to support patients’ engagement in lifestyle change. No additional SHD is delivered outside the study protocol.

Each session lasts approximately 60–90 min and includes:Visualization of individual cardiovascular and metabolic risk using the health curve, a graphical and pedagogical tool that integrates multiple lifestyle factors and biological risk markers into a color-coded risk profile (green to red), used to facilitate risk communication and support the person-centered health dialogue [34]A person-centered dialogue guided by motivational interviewing principles, focusing on autonomy, risk awareness, goal setting, and realistic behavioral change

### Control condition

Participants allocated to the control group will receive TAU provided at the forensic psychiatric clinic. TAU consists of multidisciplinary psychiatric care delivered according to individual clinical needs and may include pharmacological treatment, psychological support, occupational therapy, physiotherapy, social work, and other rehabilitation interventions. Health-related and lifestyle issues may be addressed as part of routine clinical care when considered clinically appropriate. However, participants in the control group will not receive SHD or the individualized cardiovascular risk visualization included in the intervention but will undergo the same assessments at baseline, 6 months, and 12 months as the intervention group.

### Assessments

Assessments are conducted at baseline, 6-month follow-up, and 12-month follow-up and include:Anthropometric measurements (body weight, height, BMI, waist-to-hip ratio) [35–37]Blood pressure measurementBlood sampling (fasting plasma glucose, HbA1c, lipid profile)A structured lifestyle questionnaire covering physical activity, diet, tobacco use, and alcohol consumptionHealth-related quality of life assessed using EQ-5D-5L [38–40]Mental fatigue assessed using the Mental Fatigue Scale (MFS) [41, 42]

These assessments are performed independently of the intervention sessions and are used to evaluate changes in cardiometabolic risk and lifestyle factors over time.

### Outcome measures

Outcome measures are derived from the assessments described above and are summarized in Table 1. A key exploratory outcome is change in the health curve, as described above. For analytical purposes, improvement in the health curve is defined as a shift of at least one risk category between baseline and follow-up.

**Table 1 Tab1:** Study aims, objectives, and outcome measures in the FOR-HEALTH feasibility trial

Research question/aim(s)	Objectives	Outcomes
Primary	To assess the acceptability and feasibility of the research trial, including associated processes related to the intervention and assessments	Recruitment rates; follow-up retention and questionnaire/outcome response rates; adherence to Structured Health Dialogue sessions; completeness of data collection; assessment of safety (SAEs)
Secondary	Physical health: metabolic and cardiovascular risk factors Mental health: quality of life and mental fatigue Behavioral: lifestyle behaviors	BMI; blood pressure; waist–hip ratio; fasting glucose and HbA1c; lipid profile; EQ-5D-5L; Mental Fatigue Scale; physical activity, diet, tobacco and alcohol use
Tertiary	To inform the design of a future definitive randomized controlled trial	Feasibility parameters; variability and preliminary estimates of outcomes; data completeness and acceptability of outcome measures

*BMI* body mass index, *HbA1c* glycated hemoglobin, *EQ-5D-5L* EuroQol 5 Dimensions 5 Levels, *SAEs* serious adverse events

### Data collection and assessment schedule

The timing of enrollment, intervention delivery, and outcome assessments is illustrated in the SPIRIT schedule (Fig. 2).

**Fig. 2 Fig2:**
[figure not shown]
SPIRIT schedule of enrollment, intervention delivery, and outcome assessments in the FOR-HEALTH feasibility trial. SHD Structured Health Dialogue, TAU treatment as usual, BMI body mass index, HbA1c glycated hemoglobin

### Sample size and statistical analysis

#### Sample size rationale

This study is designed as a randomized controlled feasibility trial with primary objectives focused on recruitment, retention, acceptability, intervention delivery, and completeness of data collection in compulsory forensic psychiatric care and a secondary, explorative evaluation of intervention impact on clinical outcomes. A total of 50 participants (25 per group) will be recruited.

A formal sample size calculation was undertaken based on a clinically meaningful change in the health curve, in order to evaluate a potential impact of the intervention on clinical outcomes related to the secondary, exploratory aim. Consistent with prior evaluations of the SHD model, a clinically relevant response was defined as a priori as an improvement of at least one risk category between baseline and follow-up. The proportion of participants achieving such an improvement was conservatively assumed to be 0% in the control group and 30% in the intervention group. Using a two-sided significance level of 5% (*α* = 0.05) and a power of 90% (1 − *β* = 0.90), this corresponds to a required sample size of 25 participants per group.

Although this calculation indicates that the planned sample allows preliminary exploration of change in this outcome, the study is not intended to provide conclusive evidence of effectiveness. Analyses of clinical outcomes will therefore be interpreted as exploratory and used to inform the design of a future definitive randomized controlled trial.

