#### Statistical analysis

Analyses will be conducted using Stata (StataCorp, College Station, TX, USA) and will follow the intention-to-treat principle.

Feasibility outcomes, including recruitment, retention, intervention adherence, and data completeness, will be summarized using descriptive statistics with corresponding 95% confidence intervals.

Continuous outcomes will be analyzed using linear mixed-effects models, including fixed effects for group, time, and group-by-time interaction, and random effects to account for within-subject correlation over time. Where appropriate, model assumptions will be assessed and alternative analytical approaches considered if necessary.

Results will be presented as estimated effect sizes with 95% confidence intervals. Given the feasibility nature of the study, no formal hypothesis testing is planned, and *p *values will be interpreted with caution.

Given the study design, analyses of secondary outcomes are exploratory and are not intended to evaluate intervention effectiveness. Instead, they are intended to estimate outcome variability and to inform the design, outcome selection, and sample size calculation of a future definitive randomized controlled trial. The extent, pattern, and completeness of outcome data will be described for each outcome and follow-up assessment and will be considered when interpreting the feasibility of the study procedures.

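### The 0% control improvement rate is called conservative but is the most favourable value possible, so the stated 90% power is conditional on no control improvement

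*Protocol article*

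**What the plan says.** The Sample size rationale of the protocol article bases its calculation on the health curve. A responder is a participant with "an improvement of at least one risk category between baseline and follow-up". The response proportions are "conservatively assumed to be 0% in the control group and 30% in the intervention group". With a two-sided 5% level and 90% power, the text concludes that "this corresponds to a required sample size of 25 participants per group", and the planned recruitment is the same number: "A total of 50 participants (25 per group) will be recruited". No formula or test is named, and no data are cited for the 0%. The reference there to prior evaluations of the dialogue model supports the definition of response, not the control rate.

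Two other places bear on this. Under Control condition, the article says of treatment as usual: "Health-related and lifestyle issues may be addressed as part of routine clinical care when considered clinically appropriate". Under Limitations (Feasibility-oriented primary aim), it says that "a power calculation was performed to enable detection of changes in selected secondary outcomes", before adding that the trial is mainly about feasibility and that clinical findings call for caution. The Statistical analysis section states that "no formal hypothesis testing is planned".

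**The concern.** A conservative planning assumption makes the required sample larger or the claimed power smaller. A control rate of 0% does the opposite, because it removes the control arm's variance and, with the intervention rate fixed at 30%, makes the difference as large as it can be.

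The protocol's own description makes exactly 0% hard to take for granted. Controls receive multidisciplinary care that may touch on lifestyle, they are assessed three times, and the endpoint is a shift of one category on a composite profile, which measurement variation can also produce.

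This calculation is the only quantitative rationale for 25 per group. A reader told that the assumption is conservative will take 90% as a floor when it is a ceiling under the formula that yields 25. A flat health-curve result could then be given too much weight, and the label could be carried into the planning of the definitive trial.

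**Working it through.** **Inputs** (Sample size rationale): control rate p0 = 0; intervention rate p1 = 0.30; two-sided α = 0.05 (z = 1.960); power 0.90 (z = 1.282); n = 25 per group.

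**Step 1: reproduce the plan's figure.** Unpooled normal approximation:

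n = (1.960 + 1.282)² × [p0(1−p0) + p1(1−p1)] / (p1−p0)² = 10.507 × (0 + 0.21) / 0.09 = 24.5, rounded up to 25.

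Power at n = 25: the standard error is √(0.21/25) = 0.0917, so 0.30/0.0917 = 3.273 and Φ(3.273 − 1.960) = 90.5%.

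The stated number therefore reproduces. The formula is inferred from the match. Other methods at 0% versus 30% give:
- pooled variance: 28 per group, or 86.7% power at 25;
- Fisher's exact test at 25 per group: 80.7% power by enumeration;
- uncorrected chi-square at 25 per group: 96.7% power by enumeration.

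**Step 2: in which direction does 0% push?** With p1 fixed at 0.30, raising p0 shrinks the numerator p1−p0 and adds p0(1−p0) to the variance, so both effects lower power. If the 30-point difference is held instead, the variance sum is 0.21 at 0% vs 30%, 0.275 at 5% vs 35% and 0.33 at 10% vs 40%, so power again falls from its value at 0%. No control rate gives more power than 0% on either basis.

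**Step 3: size of the effect.** Power = Φ((p1−p0)/√{[p0(1−p0)+p1(1−p1)]/25} − 1.960). The non-zero control rates are assumptions, since the document gives none. In the middle scenario, background improvement acts in both arms and the intervention adds a response in 30% of those who would not otherwise improve: p1 = p0 + 0.30(1−p0).

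| Control rate | Intervention stays at 30% | Same background in both arms | 30-point difference kept |
|---|---|---|---|
| 0% | 90.5% | 90.5% | 90.5% |
| 5% | 69% | 78% (vs 33.5%) | 82% (vs 35%) |
| 10% | 45% | 66% (vs 37%) | 74% (vs 40%) |
| 15% | 25% | 56% (vs 40.5%) | 69% (vs 45%) |

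Example, 5% vs 30%: variance sum 0.0475 + 0.21 = 0.2575; standard error √(0.2575/25) = 0.1015; 0.25/0.1015 = 2.463; Φ(0.503) = 69%.

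At smaller rates with the intervention at 30%, power is 83% for a 2% control rate and 74% for 4% (one expected improver in 25). The half-point of slack that comes from rounding 24.5 up to 25 is gone, by linear interpolation between 0% and 2%, at a control rate of about 0.15%: (90.5 − 90)/(90.5 − 83.2) × 2% ≈ 0.15%.

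**Step 4: does the method change the picture?** At 5% vs 30%, exact power is 55% (Fisher) or 71% (uncorrected chi-square). At 10% vs 30% it is 30% or 45%. The level depends on the test, but the direction does not.

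All figures take 25 analysed per group, which is also the number to be recruited.

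**The case against.** The strongest reply is that the figure decides nothing. The calculation belongs to a secondary, exploratory aim. Clinical results are to be reported as estimates with confidence intervals, and the article asks for cautious reading in the limitations, the sample size rationale and the analysis section. The primary outcomes (recruitment, retention, adherence, completeness, safety) do not depend on the control improvement rate, and the trial will observe that rate for itself before the definitive study is sized. This stands, and it limits the severity. It does not make the word *conservatively* correct, and it does not attach the missing condition to the 90%.

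A second reply is that treatment as usual, repeated assessment and measurement noise act in both arms, so holding the intervention arm at 30% while only controls improve is the worst case. This also stands. The left-hand power column should not be quoted alone, which is why three scenarios are given.

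A third is that the likely control rate is unknown. The documents give no number of categories, distribution or test-retest correlation. Simulated chance reclassification ranges from about 5% to 21%, depending on whether categories are assumed equally filled or 70–80% of patients are in the worst one, and on a correlation of 0.95 or 0.90. That noise makes exactly 0% unlikely, but no particular rate can be claimed.

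A reader might infer that power collapses as soon as any control participant improves. The figures do not support that. Power depends on the underlying rate and is still about 74% at 4%. With one observed control improver, Fisher's test needs 7 intervention improvers to reach significance instead of 6.

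**Conclusion.** Wrong as written, with minor to moderate consequence. The 0% control rate is the most favourable value possible and is not conservative. The 90% holds only at 0% versus 30%, under an inferred unpooled approximation with all 25 per group analysed. Any non-zero control rate lowers it under that formula. At assumed control rates of 5% to 15%, power runs from about 69% down to 25% with the intervention rate fixed at 30%, from 78% to 56% with background improvement in both arms, and from 82% to 69% with the 30-point difference kept.

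It may be tempting to conclude that the trial is too small or that its sample size is miscalculated. The documents do not support either conclusion: the arithmetic for 25 is right for the stated inputs, the trial is a feasibility study, no formal test is planned on this outcome, and the primary aim is untouched.

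**What to change.** Keep 50 participants. In the Sample size rationale, delete *conservatively* and replace the unqualified power statement with wording such as:

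> With 25 participants analysed per group, power is 90% (unpooled normal approximation, two-sided 5%) if no control participant improves and 30% of the intervention group does. For illustrative control rates of 5%, 10% and 15%, power is about 69%, 45% and 25% if the intervention rate stays at 30%; about 78%, 66% and 56% if the same background improvement also occurs in the intervention group; and about 82%, 74% and 69% if the 30-point difference is kept.

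If another formula or test was used, name it and recompute these figures. If data support a 0% control rate, cite them. In the limitations, under Feasibility-oriented primary aim, reword the opening clause so that it no longer says without qualification that the calculation enables detection of changes in secondary outcomes.

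The cost is wording only. The stated power becomes less favourable; no participants, visits or analyses are added.

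### The 90% power for 25 per group is calculated at the most favourable control rate, which the text calls conservative, and the limitations section extends it to several outcomes

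*Protocol article*

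**What the plan says.** The Sample size rationale defines response on the health curve as "an improvement of at least one risk category between baseline and follow-up". The two response rates are "conservatively assumed to be 0% in the control group and 30% in the intervention group". With two-sided alpha of 5% and power of 90%, it concludes that "this corresponds to a required sample size of 25 participants per group". Planned recruitment equals that number: "A total of 50 participants (25 per group) will be recruited". Neither a formula nor a test is named. The same section calls the clinical analyses exploratory, and the Statistical analysis section adds that "no formal hypothesis testing is planned".

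The limitations paragraph on the feasibility-oriented primary aim describes the calculation more broadly: "a power calculation was performed to enable detection of changes in selected secondary outcomes".

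**The concern.** Three features make the 90% look firmer than it is.

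- A control rate of exactly 0% removes all variance from one arm, where a normal approximation is least dependable.
- For a given intervention rate, 0% is also the control rate that maximises power. Calling it conservative points the reader the wrong way. The Control condition section says that lifestyle issues may be addressed in routine care, so a few improvers on usual care are plausible.
- The limitations paragraph turns a calculation for one binary outcome into a statement about several secondary outcomes.

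This calculation is the only quantitative basis given for N = 50. A reader who takes it at face value could read an unremarkable health-curve result, or one on BMI or HbA1c, as better supported than it is.

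**Working it through.** **Inputs** (Sample size rationale; 1:1 allocation from Study design and setting): control 0, intervention 0.30, two-sided alpha 0.05, power 0.90, 25 per group. The control rates of 2% and 4% below are assumptions; 4% is one responder in 25.

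**1. Reproducing the stated figure.** Here (z₀.₉₇₅ + z₀.₉₀)² = (1.960 + 1.2816)² = 10.507.

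- Unpooled: 10.507 × (0 × 1 + 0.3 × 0.7) / 0.3² = 10.507 × 0.21 / 0.09 = 24.5, so **25**. This matches.
- Pooled under the null: (1.960 × √(2 × 0.15 × 0.85) + 1.2816 × √0.21)² / 0.09 = 27.6, so 28.
- Pooled with continuity correction: 34.
- Pooled variance in both terms: 29.8. Arcsine: 15.6.

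Only the unpooled version gives 25 under the stated two-sided alpha. That it was the formula used is an inference.

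**2. Power at 25 per group, 0% against 30%.** With no control responders, each test rejects once the intervention arm has enough responders, so power is a binomial tail for Bin(25, 0.3).

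| Test | Rejects from | p at that boundary | Power |
|---|---|---|---|
| Fisher's exact | 6 vs 0 (5 vs 0 gives p = 0.0502) | 0.022 | 80.7% |
| Boschloo's exact | 5 vs 0 | 0.033 | 91.0% |
| Barnard's exact | 4 vs 0 | 0.041 | 96.7% |
| Uncorrected Pearson | 4 vs 0 | 0.037 | 96.7% |

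**3. Non-zero control rate, intervention held at 30%.** Power is the sum of Bin(a; 25, p_c) × Bin(b; 25, 0.3) over all outcomes with b > a and p ≤ 0.05.

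| Control rate | Fisher | Pearson |
|---|---|---|
| 0% | 80.7% | 96.7% |
| 2% | 71.5% | 87.2% |
| 4% | 60.5% | 76.4% |

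**4. The same direction from the formula that reproduces 25.**

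- At 2%: n = 10.507 × (0.21 + 0.0196) / 0.28² = 30.8, so 31. Power at 25 is Φ(0.28 / √(0.2296/25) − 1.960) = Φ(0.96) = 83%.
- At 4%: n = 10.507 × (0.21 + 0.0384) / 0.26² = 38.6, so 39. Power at 25 is Φ(0.26 / √(0.2484/25) − 1.960) = Φ(0.65) = 74%.

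Holding the difference at 30 points instead does not change the direction: for 4% against 34%, n = 10.507 × (0.0384 + 0.2244) / 0.09 = 30.7, so 31.

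**5. Scope of the calculation.** The Sample size rationale uses one outcome, the health curve. The article shows no power calculation for any other secondary outcome, whereas the limitations sentence is plural.

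**The case against.** A reader might infer that the stated power is simply overstated, because Fisher's exact test gives 81%. The document does not support that. The 25 follows from its own inputs by a recognised formula, so there is no arithmetic error. Fisher's test is not planned, and the test may be left to an analysis plan that is not shown. Under the stated 0% and 30%, two unconditional exact tests give 91.0% and 96.7%. Fisher's figure is also partly discreteness: at 24 per group its p value for 5 vs 0 is 0.0496 and its power 88.9%, so adding one participant per arm lowers power by about 8 points.

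It can also be said that 'conservatively' was meant for the 30%, and that over-reading is already guarded against. The study disclaims conclusive evidence of effectiveness, asks for caution on clinical outcomes, and plans estimates with confidence intervals.

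Most of this stands. It rules out the stronger claim and keeps the severity low. It does not rescue the wording: the sentence attaches 'conservatively' to both rates, and for the control rate the direction is wrong whichever test is used. Nor does it explain the plural in the limitations paragraph.

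**Conclusion.** The point holds as a minor correction to a stated figure. The 25 per group is reproducible, but the 90% is attained only under the control rate most favourable to power, and even there the answer ranges from 80.7% to 96.7% with the test. At an assumed 2% control rate both Fisher and Pearson fall below 90% (71.5% and 87.2%), as does the formula that reproduces 25 (83%). At 4% the range is 60.5% to 76.4%.

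These figures assume that all 25 per group are analysed and that 30% of the intervention arm improves. The 2% and 4% are illustrations, since the article gives no data on improvement under usual care. At 1% the answer still depends on the test (Fisher 76%, Pearson 92%).

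The limitations sentence claims more than was calculated. Neither matter affects the feasibility outcomes or calls for a different sample size.

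**What to change.** Keep N = 50. In the Sample size rationale, delete 'conservatively' and 'required', name the formula or test behind the power figure, and add power at a non-zero control rate. For example: *With 25 analysed per group and 30% improving in the intervention group, power at two-sided 5% is 80.7% (Fisher's exact test) to 96.7% (uncorrected Pearson test) if no control participant improves, 71.5% to 87.2% if 2% do, and 60.5% to 76.4% if 4% do.* If the authors have already settled on one test, its figures alone are enough. The range is not a reason to prescribe a particular test.

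In the limitations paragraph on the feasibility-oriented primary aim, replace the plural reference to secondary outcomes with *one exploratory outcome, the health curve*.

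The cost is wording only: no extra participants and no change to the planned analyses. The stated power becomes less favourable.
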